## Abstract

**Background:**

Post-covid syndrome is an emerging condition involving a wide range of symptoms, including high rates of poor mental health. The diagnostic relevance and clinical severity of these symptoms are largely unknown, and evidence for treatment of post-covid mental health symptoms is lacking. This protocol describes a pilot randomized clinical trial, primarily aiming to assess feasibility, participant adherence and satisfaction in a novel phycho-therapeutic intervention on post-covid anxiety and depression symptoms ≥1 year after critically ill COVID-19. Whether the intervention may generate improvements in post-covid depression, anxiety, post-traumatic stress and health-related quality of life (HRQoL) will be addressed in a following larger trial.

**Methods:**

A multicenter, investigator-initiated randomized controlled trial (Clinical Trial Identifier number NCT05119608) including Intensive Care Unit (ICU)-treated COVID-19 survivors, who display symptoms of anxiety and/or depression at follow-up 12 months after hospitalization (Hospital Anxiety and Depression Scale ≥8 for depression or anxiety). Eligible individuals are referred to a psychiatrist for structured diagnostic assessment and inclusion in the trial. Participants will be randomized to either a 10-week cognitive behavioral therapy intervention with added acceptance and commitment therapy (CBT-ACT) or standard care (primary care referral). Primary study outcome measure is feasibility and patient adherence, defined as the proportion of participants who consent to randomization and remain in the study including follow-up. Secondary outcome measures include reduced symptoms in the HADS depression/anxiety subscales, post-traumatic symptoms, HRQoL and user satisfaction at 3 months after the intervention.

**Discussion:**

This protocol describes a pilot trial to assess feasibility and preliminary effects of a structured psycho-therapeutic intervention to ameliorate mental health in a population severely affected by COVID-19, where evidence for structured psycho-therapy is lacking.

## Introduction

### The COVID-19 Pandemic and Mental Health

The coronavirus disease, COVID-19, has had a devastating impact on public health, with persisting symptoms after the acute infection in a substantial number of patients. This is typically referred to as a post-covid syndrome, characterized by several symptoms affecting quality of life (1–5). Mental health symptoms are common in reports of a post-covid syndrome (4, 6). Studies have shown persistent symptoms of clinical depression in up to 40 percent at 1-6 months after COVID-19 in patients treated either in hospital or at home (7), whereas lower rates of depression (15 percent) also have been reported after hospitalization for COVID-19 (8).

Specific features of the COVID-19 disease itself have been suspected to cause mental health problems (9–12), in addition to possible causes emerging from societal changes during the pandemic (13, 14). Neuro-cognitive symptoms in COVID-19 have been associated with risk of post-covid depression and anxiety (15), and inflammatory parameters are suggested to have a role in neurological, cognitive and mental disorders in COVID-19 (7).

### Post-covid Mental Health Symptoms in Post-ICU COVID-19 Survivors

It has been reported that people surviving the acute phases of a severe COVID-19 condition requiring intensive care are at high risk of developing mental health symptoms.

In a large cohort of COVID-19 patients, severity of illness was associated with worse pulmonary function at 6-month follow-up, and anxiety and depression were significantly more common among the critically ill than among other less severely ill COVID-19 survivors (32 percent vs. 22–23 percent). Other common findings were fatigue, muscle weakness and sleeping disorders (2). Likewise, post-traumatic stress symptoms have been reported to be twice as high in ICU-treated COVID-19 survivors compared to hospital-treated non-ICU patients with COVID-19 (16). One study demonstrated that a substantial proportion of post-critically ill COVID-19 patients had mental health problems after a median of 5 months. In particular, depression, anxiety, and post-traumatic stress were common, occurring in 33–36 percent (17). 6-month prevalence of depression, mood or psychotic disorders was seen in 28 percent of ICU-treated COVID-19 patients in a recent study, compared to 24 and 25 percent of non-hospitalized, and non-ICU-treated hospitalized patients (18). Thus, although there is data pointing toward a narrow difference in mental health consequences between ICU-treated and other COVID-19 patients (18), there is still reason to believe that severity of disease in COVID-19 is associated with long-term mental health problems.

### Research Gaps in Clinical Significance and Treatment of Post-covid Mental Health Symptoms

There is a relatively high frequency of poor mental health in the post-covid syndrome, and particularly in patients surviving severe COVID-19 requiring intensive care. However, follow-up studies of post-covid syndrome cohorts have so far, with few exceptions, included symptom descriptions rather than diagnostic constructs (11), and there is a lack of studies assessing interventions. To our knowledge, the only intervention study of post-covid mental health problems to date, is from Mazza and co-workers (19), demonstrating a significant effect of antidepressant medications in post-COVID-19 patients, but the study had no control group and a short follow-up.

Given the complexity and novelty of the post-covid syndrome and the uncertainty about pathological mechanisms and the long-term course, there is an urgent need for structured diagnostic understanding and need to incorporate mental health issues in structured follow-up and treatment of the condition (20). This includes development of structured diagnostic and interventional efforts (6) for post-covid mental health problems. Successful treatment of mental health symptoms in COVID-19 survivors is likely to require an understanding of the background of these symptoms and of the complexity of mental health suffering in combination with a severe physical condition. Acceptance and commitment therapy (ACT), originating from a cognitive behavioral therapy (CBT)-oriented framework, has been suggested as an intervention for other conditions where mental health symptoms develop in the context of a physical disorder. CBT/ACT (21) is well-suited for psychotherapy in situations where mental health problems occur in the context of a physical disease, or other complex conditions. This type of psycho-therapy is less commonly provided than standard CBT, but it is well-established and is part of the overall umbrella of interventions based on the core features of CBT, particularly in the context of specific, more complex conditions. This includes treatment of chronic pain (21), advanced malignant disease (22), or fibromyalgia (23). Likewise, the method has been suggested for the promotion of healthy lifestyle interventions (24) and occupational rehabilitation in patients on sick leave (25).

An additional research gap is whether a psycho-therapeutic treatment approach is feasible and accepted by patients with a history of critical illness due to COVID-19 infection. Thus, there is reason to investigate feasibility including adherence as well as user satisfaction with a psycho-therapeutic treatment initiated within the multi-disciplinary framework of COVID-19 rehabilitation and follow-up. The purpose of the present study is to assess long-term mental health symptoms in individuals who have survived critical COVID-19 requiring intensive care, and to scientifically test the feasibility of an integrated and adapted psycho-therapeutic intervention against mental health symptoms.

### Specific Aims

The present study aims to

a) Examine whether Acceptance and Commitment Therapy, based on the base framework of Cognitive Behavioral Therapy (CBT-ACT), compared to standard clinical care (referral to primary care), is feasible in critically ill COVID-19 survivors at12 months after ICU care, assessed by consent rate, recruitment success and protocol adherence (retention and successful follow-up rates).b) Explore the diagnostic entities and clinical significance of the mental health symptoms reported in ICU-treated COVID-19 survivors at 12 months after ICU care.c) Evaluate whether Cognitive Behavioral Therapy with Acceptance and Commitment Therapy (CBT-ACT), compared to standard clinical care (referral to primary care) has beneficial effects for amelioration of depression, anxiety, post-traumatic symptoms, fatigue, and for improvements of quality of life.

## Methods

### Study Population and Setting

The present study will include individuals after intensive care, in two Swedish settings; four ICUs in the Skåne Region (southern Sweden) and two ICUs at Södersjukhuset (Region Stockholm). Surviving individuals admitted to ICU-care are invited to a structured follow-up after 12 months, including self-reported questionnaires regarding mental health problems. The 12-month follow-up measures are carried out through physical (or telephone) follow-up visits (Region Skåne) or through questionnaires sent by regular mail (Stockholm study site). COVID-19 survivors who screen positively for clinical anxiety or depression, defined as a score of ≥8 on either of the two sub-scales within the questionnaire HADS (26), are invited to take part in the study. Eligible individuals will then undergo a structured online clinical diagnostic assessment by a physician experienced in clinical psychiatry. The structured psychiatric medical assessment is guided by the Mini Neuropsychiatric Interview [MINI, (27)]. The MINI interview provides preliminary, structured diagnoses according to the diagnostic manual of the American Psychiatric Association, the DSM-5 [American Psychiatric Association, (28)]. The sections chosen for this assessment include those related to major depression, generalized anxiety disorder, and post-traumatic stress. In addition to the abbreviated MINI assessment, a non-structured clinical interview and broad diagnostic assessment will be performed.

After the assessment, eligible ICU survivors will be offered to enter the study. Consenting participants will be randomized on an equal basis (1:1) to the intervention or control arm. Randomization will be carried out from concealed, opaque envelopes, containing randomization or control assignment as based on a computer-generated randomization list [random.org, (29)], handled by a secretary not involved in the research project. Exclusion criteria, assessed upon the medical examination, include conditions in which participants are acutely suicidal, psychotic, suffering from a mental disorder requiring in-patient psychiatric treatment, opposed to receiving a psycho-therapeutic intervention, or with cognitive problems or language difficulties which are judged to be too extensive for the informed consent procedure and for a psycho-therapeutic intervention.

### The Intervention

A structured, 10-session psycho-therapeutic intervention, typically occurring once weekly, will be performed (with a possibility to adjust the frequency). The therapy is based on cognitive behavioral therapy (CBT), with the addition of a therapeutic model of acceptance and commitment therapy (ACT) provided by clinical therapists with standard CBT training and extensive experience of complex mental health disorders. The intervention will be provided face-to-face whenever possible, with an alternative to offer the intervention online in case of practical difficulties or circumstances making an online meeting more convenient for the participant.

The control group (comparator) will consist of a referral to primary care (general practitioner) for medical assessment and support. The control condition is expected to provide at least the same level of support and care as in everyday, non-research-related, clinical care.

### Outcomes

The primary outcome is to test if the psycho-therapeutic treatment approach is feasible in critically ill COVID-19 survivors at 12 months after ICU care, defined as the proportion of participants who consent to randomization and remain in the study including follow-up. Secondary outcome measures include reduced symptom burden in the HADS depression and anxiety subscales, post-traumatic symptoms and mental health-related quality of life (HRQoL), as well as users' experience and user satisfaction. Secondary outcome measures (Table 1) are included both in the 12-month assessment prior to randomization, as well as in repeated assessments at 3 months after randomization (2 weeks after treatment ending in the intervention group), 3 months after the completion of the intervention, and in a longer perspective (12 months after intervention/control), administered by an as outcome assessor blinded to the intervention arm. Participants' experience and satisfaction of the CBT-ACT intervention will be assessed 2 weeks after the intervention (for the randomized intervention group only).

**Table 1 T1:** Outcome assessments at baseline and follow-up.

**Outcome**	**Outcome assessment**	**Baseline variables**	**Study population 12 months post-ICU-care**	**Follow-up 2 weeks after intervention**	**Follow-up 3 months after intervention**	**Follow-up 12 months after intervention**
Mental health	Hospital Anxiety and Depression Scale (HADS)		X	X	X	X
	Post-Traumatic Stress Disorders Checklist for DSM-5 (PCL-5)		X	X	X	X
Fatigue	Modified Fatigue Impact Scale (MFIS)		X	X	X	X
Health related Quality of Life	SF-36-v2 (full scale and mental health sub-scale)		X	X	X	X
Participants' satisfaction	Satisfaction with Therapy and Therapist Scale (STTS)			X (intervention group only)		
Demographic background data	Age, gender	X				
Clinical baseline information	Severity of disease on arrival (Simplified Acute Physiology Score3, SAPS3)	X				
	Progression of disease severity in the ICU (30) including Sequential Organ Failure Assessment (SOFA)	X				
	Severity of ARDS on admission and daily,	X				
	Time (days) in the ICU	X				
	Invasive/non-invasive mechanical ventilation (yes/no)	X				
	Time on ventilator (days)	X				
Self-reported psychiatric information	Previous mental health disorders		X			

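### The primary feasibility proportion merges consent with retention in both arms, leaves its denominator and visit open, and omits therapy attendance, so by itself it cannot show that CBT-ACT is feasible

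*Protocol article*

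**What the plan says.** The Outcomes section states the purpose: "The primary outcome is to test if the psycho-therapeutic treatment approach is feasible in critically ill COVID-19 survivors". It then gives the measure as one figure, "defined as the proportion of participants who consent to randomization and remain in the study including follow-up". The Methods part of the Abstract uses the same figure and labels it as adherence too: "Primary study outcome measure is feasibility and patient adherence, defined as the proportion of participants who consent to randomization and remain in the study".

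Specific Aims, aim (a), puts feasibility differently. It sets CBT-ACT against standard care, with feasibility "assessed by consent rate, recruitment success and protocol adherence (retention and successful follow-up rates".

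Three other statements bear on how the figure behaves:

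- Study Population and Setting: "Consenting participants will be randomized on an equal basis (1:1) to the intervention or control arm". Consent therefore comes before allocation.
- The Intervention: "A structured, 10-session psycho-therapeutic intervention, typically occurring once weekly, will be performed (with a possibility to adjust the frequency".
- The Intervention, on the comparator: "The control group (comparator) will consist of a referral to primary care (general practitioner) for medical assessment and support".

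The Outcomes section and Table 1 plan three follow-ups: 2 weeks, 3 months and 12 months after the intervention. The article makes neither attendance at the sessions nor completion of therapy an outcome at any level. Satisfaction with therapy is a secondary outcome, collected in the intervention arm only.

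**The concern.** The defined primary figure and the question put to it do not fit, for four reasons.

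1. **Two steps in one number.** Willingness to be randomised and staying in the study are different processes with different remedies. Consent precedes allocation, so a figure that includes it cannot be split by arm, although aim (a) is framed as a comparison with standard care.
2. **Both arms count.** Nothing restricts the figure to the CBT-ACT arm. A control who is referred to primary care and returns the questionnaires counts towards the feasibility of a therapy that he or she never received.
3. **Denominator and visit are open.** The base could be those invited after a positive HADS screen, those found eligible and offered the study, or those randomised. Follow-up could mean any of three visits.
4. **Uptake is absent.** Someone allocated to CBT-ACT who attends no session but answers the questionnaires counts as a success.

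Strengths and Limitations and Conclusions both say that the results will serve as the basis for a larger, adequately powered trial. Planning that trial needs consent, retention by arm and therapy uptake as separate quantities. The defined primary figure supplies none of them separately, unless its base is those randomised, when it is retention pooled over the arms.

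**Working it through.** The plan has no figure to reproduce. Data Analysis and Statistics gives a convenience sample of at least 40, with no target proportion or dropout rate. The check therefore asks how the defined figure behaves.

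**Inputs.** From the article: 40 randomised, 1:1, so 20 per arm; 10 sessions; three follow-ups. Assumed, because the article gives no counts: 50 or 80 people offered the study, 32 retained, and the splits shown below. Intervals are exact (Clopper-Pearson) 95%.

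**Formulas.** Consent C = randomised / offered. Retention R = retained / randomised. Composite P = C × R = retained / offered. If the base is those randomised, C = 1 by construction and P = R.

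**Step 1: the denominator.** The same 32 retained people give:

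| Base | P | 95% CI |
|---|---|---|
| 40 randomised | 32/40 = 80% | 64–91% |
| 50 offered | 32/50 = 64% | 49–77% |
| 80 offered | 32/80 = 40% | 29–52% |

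**Step 2: merging.** P = 60% arises from C × R = 60% × 100%, 75% × 80%, 90% × 66.7% or 100% × 60%. The value alone cannot tell refusal from dropout.

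**Step 3: pooling the arms.** With 50 offered and 40 randomised:

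| Retained, CBT-ACT + control | P | CBT-ACT retention (95% CI) |
|---|---|---|
| 16 + 16 | 32/50 = 64% | 16/20 = 80% (56–94%) |
| 12 + 20 | 32/50 = 64% | 12/20 = 60% (36–81%) |
| 20 + 12 | 32/50 = 64% | 20/20 = 100% (83–100%) |

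**Step 4: attendance.** Sessions attended do not enter P. With 32 of 50 retained, P stays at 64% for every row:

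| CBT-ACT participants completing therapy | Proportion (95% CI) |
|---|---|
| 0/20 | 0% (0–17%) |
| 4/20 | 20% (6–44%) |
| 10/20 | 50% (27–73%) |
| 16/20 | 80% (56–94%) |
| 20/20 | 100% (83–100%) |

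Completing therapy and remaining in the study are separate events: a person can do either without the other.

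**Step 5: can the separate measures be estimated at this size?** Consent would be 40/50 = 80% (66–90%) or 40/80 = 50% (39–61%). Overall retention would be 32/40 = 80% (64–91%). Measures within one arm of 20 carry roughly ±20 percentage points, as the intervals in Steps 3 and 4 show. That is coarse, but it answers the question asked.

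**The case against.** The strongest reply is that the Outcomes wording is shorthand. Aim (a) lists the components, and Data Analysis and Statistics refers to feasibility measures in the plural. The team can report consent and retention by arm from participant flow data that it must hold anyway. Satisfaction scores in the intervention arm add indirect evidence of acceptability. This stands, and it limits the point to the defined primary proportion. A reader might infer that the trial cannot show feasibility at all, or that the larger trial must be planned on one merged number; the documents do not support either inference.

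A reader might also infer that any value would pass because no progression cut-off exists. That cannot be known. This is a journal article, and cut-offs may stand in the full protocol or analysis plan, which are not shown. The point does not rest on them.

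It can also be said that aim (a) deliberately equates protocol adherence with retention and follow-up, and that a pilot for a two-arm trial must know whether both arms can be retained. Both are fair. But they do not justify using the figure to test whether the treatment approach is feasible, or the Abstract's wording, "Primary study outcome measure is feasibility and patient adherence".

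On timing, the Abstract and Study Variables point to 3 months after the intervention, but for secondary outcomes. The primary outcome is still tied to no visit.

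**Conclusion.** The point holds for the primary outcome as defined in the Abstract and in Outcomes. It is one proportion with no stated base and no named visit. It merges consent with retention, pools the arms, does not match aim (a) and does not respond to therapy uptake. By itself it cannot show that CBT-ACT is feasible, and it does not support the adherence label.

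The size is illustrative. The same assumed data read as 80%, 64% or 40% depending on the base, and none of these moves as completion in the CBT-ACT arm goes from 0 to 20 of 20. The counts offered, retained and completing are assumptions. The insensitivity to attendance does not depend on them, because attendance is not in the definition.

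This should be fixed, but it does not invalidate the trial. It is a pilot with a convenience sample, consent and retention by arm are recoverable, and satisfaction is collected. Session attendance is the one component for which the article defines no measure.

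**What to change.** Reconcile the Abstract, Specific Aims and Outcomes. Replace the single proportion with co-reported measures, each with its denominator and 95% CI:

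1. **Consent** = randomised / found eligible and offered the study after the psychiatric assessment. Report alongside it the flow from HADS-positive and invited to eligible, with reasons for exclusion. Using everyone invited as the base would count people excluded at assessment as refusals. The reasons matter because people opposed to psychotherapy are excluded as ineligible, which raises consent among those eligible.
2. **Retention, by arm** = followed up at one named visit, chosen from the three already planned / randomised to that arm.
3. **Therapy adherence** = CBT-ACT participants attending at least a pre-specified number of the 10 sessions / all allocated to CBT-ACT, plus the distribution of sessions attended. The participant is the unit, so a simple binomial interval applies.

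Suggested wording for Outcomes: *The primary feasibility measures are consent among eligible people offered the study, retention in each arm at [named visit], and the proportion of participants allocated to CBT-ACT who attend at least [number] of the 10 sessions. Each is reported with its numerator, denominator and 95% confidence interval.*

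Cost: no additional patients or visits. Several figures replace one. Session attendance has to be recorded; the article does not say whether it already is. Protocol and registry wording must be updated, possibly with an ethics amendment; the Ethics Statement lists two already.

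### The HADS score that selects patients is also the only pre-randomisation HADS shown: a weak baseline covariate, though the between-arm comparison is not biased

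*Protocol article*

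**What the plan says.** **Selection.** In Study Population and Setting, a positive screen at the 12-month follow-up opens the way into the trial. Survivors above the cut-off, "defined as a score of ≥8 on either of the two sub-scales within the questionnaire HADS (26), are invited to take part in the study". The score comes from a visit or telephone call in Skåne and from a postal questionnaire in Stockholm.

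**Between screening and allocation.** The same section continues: "Eligible individuals will then undergo a structured online clinical diagnostic assessment by a physician experienced in clinical psychiatry". The assessment consists of selected MINI sections and an open clinical interview. The offer to take part, consent and the envelope follow. No HADS is listed at this step and no interval is given.

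**Baseline.** In Outcomes, the secondary measures "are included both in the 12-month assessment prior to randomization" and at three later times. Table 1 agrees: HADS is marked at 12 months post-ICU and then at three follow-ups.

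**Outcome wording.** The abstract's Methods say: "Secondary outcome measures include reduced symptoms in the HADS depression/anxiety subscales". The Outcomes section likewise speaks of a reduced burden, and neither sentence says whether the reduction is within an arm or between arms.

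**Analysis.** Data Analysis and Statistics refers to comparing intervention with control by intention to treat. The adjustment factors it names are psychoactive medication history, age, sex and mechanical ventilation. Baseline HADS is not named.

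**The concern.** A score that has to reach a cut-off is, on average, too high. Measured again, the same people score lower without treatment, and some will have improved in the meantime. When the selecting score is also the baseline, two things follow.

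- A before-after reduction in either arm contains this fall. It would be easy to misread in a pilot that, according to its abstract, looks at preliminary effects.
- Selection cuts off the lower part of the score's range, and time passes before treatment starts. Both weaken its correlation with later scores, and so its value as a covariate. With about 40 participants, or 20 per arm at 1:1, baseline adjustment is one of the few sources of precision available.

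**Working it through.** The plan has no figure of its own to reproduce here. The 40 participants are a convenience target without power inputs. The cut-off of 8, the 1:1 ratio and the 40 come from the article. **All means, SDs and correlations below are assumptions.**

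**1. Fall without treatment, one subscale.** Assume mean 6 and SD 4. For whole-number scores the cut lies at 7.5.
- k = (7.5 − 6)/4 = 0.375, so 35% are selected.
- λ = φ(k)/(1 − Φ(k)) = 0.372/0.354 = 1.051. The mean of those selected is 6 + 4 × 1.051 = 10.2.
- Expected fall at retest correlation r is (1 − r) × 4 × 1.051 = 4.2 × (1 − r).

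Simulation with rounded scores bounded at 0 to 21 gives:

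| r | fall by formula | fall by simulation | below 8 at retest | correlation of the two scores among those selected |
|---|---|---|---|---|
| 0.9 | 0.42 | 0.4 | 19% | 0.73 |
| 0.8 | 0.84 | 0.9 | 27% | 0.57 |
| 0.7 | 1.26 | 1.3 | 33% | 0.46 |
| 0.6 | 1.68 | 1.7 | 39% | 0.37 |

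**2. Selection on either subscale, as the plan has it.** Assume mean 4.5 or 6, SD 4, anxiety-depression correlation 0.65 and the same range of r. Mean HADS-anxiety falls by 0.3 to 1.5 points in all those selected, and by 0.4 to 2.1 in those with anxiety at 8 or more. Between 16% and 41% are below 8 on both subscales at retest.

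**3. Effect on the randomised comparison.** In the same simulation, with no treatment effect, the between-arm difference in change is at most 0.02 points in absolute value. With 20 per arm (mean 4.5), a between-arm test at 5% rejects in 4.8% to 5.6% of trials. A before-after test within one arm rejects in 16% (r = 0.9) to 49% (r = 0.6).

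**4. Value as a covariate.** Back to one subscale with mean 6 and SD 4. Assume also that a repeat score correlates 0.7 with the outcome before selection, and that the screening score relates to the outcome only through the repeat. Let d = λ(λ − k) = 1.051 × 0.676 = 0.710, the share of screening variance removed by selection. The outcome variance left unexplained among those selected is
- with the screening score: 1 − 0.49r²(1 − d)/(1 − 0.49r²d)
- with the repeat: 1 − 0.49(1 − r²d)/(1 − 0.49r²d)

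At r = 0.9 these give 84% and 71%; at r = 0.6 they give 94% and 58%. Simulation with rounded, bounded scores gives 84% to 94% for the screening score and 72% to 59% for the repeat. The standard error of an adjusted comparison with the repeat is therefore √(72/84) = 0.93 down to √(59/94) = 0.79 times that with the screening score, or about 7% to 21% smaller.

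**The case against.** The strongest objection is that the plan compares arms. Aim (c) sets CBT-ACT against standard care, the analysis section refers to intervention versus control, and allocation is 1:1. Regression to the mean and spontaneous recovery fall equally on both arms in expectation, and no section plans a within-arm test. This stands, and step 3 bears it out. A reader might infer that the estimated treatment effect is contaminated; the documents do not support that.

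Other stronger readings also fail:

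- **Recovered patients are randomised.** No current diagnosis or symptom level is named as an entry condition. But a physician assesses each person first, and only those judged eligible are offered entry. The text does not establish that someone who is well would be randomised.
- **Clinical status at entry is unknown.** The MINI covers depression, generalised anxiety and post-traumatic stress close to entry. Only the HADS level is unrecorded. The stated feasibility measures (consent, recruitment, retention, follow-up) do not depend on it.
- **Recruitment is open-ended.** The abstract's Background speaks of "post-covid anxiety and depression symptoms ≥1 year after critically ill COVID-19", but this describes when symptoms occur and is not a recruitment window. Elsewhere the article says 12 months.

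It is also fair to say that the covariate list is introduced as including certain factors, so it may not be exhaustive, and that a fuller protocol may give the interval or a repeat HADS. However, Table 1 is the article's own schedule and shows none. Finally, reusing the screening score spares ICU survivors a questionnaire, which is a defensible choice in a pilot. These arguments lower the priority of the point without removing the gain in precision.

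**Conclusion.** The point holds as a minor one about precision and interpretation of secondary outcomes. The selecting HADS is the only pre-randomisation HADS shown, the interval to randomisation is not stated, and baseline HADS is not among the named covariates. The between-arm comparison remains valid.

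Two limits apply to the sizes. The fall of about 0.4 to 1.7 points assumes a stable population with mean 6, SD 4 and r from 0.9 to 0.6. Real recovery before treatment would add to it, and a mean or SD different from those assumed would change it. The 7% to 21% gain in standard error also depends on step 4's assumption that the screening score carries no information beyond the repeat. If it carries some, the gain is smaller. The absence of between-arm bias follows from randomisation and needs none of these assumptions.

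**What to change.** - Repeat the HADS and the other self-report symptom and quality-of-life scales in Table 1 at the existing diagnostic assessment, after consent and before the envelope is opened.
- Use the repeat as baseline covariate in the between-arm comparison. If it is not adopted, at least add the 12-month HADS already collected to the named covariates.
- Keep the 12-month score for eligibility. Entry criteria need not change.
- Report the interval from screening to randomisation and the proportion still at 8 or more on either subscale at randomisation.
- State that symptom effects are interpreted as between-arm differences only.

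The cost is a few minutes of questionnaire time per participant at a contact that already takes place. One consequential edit is needed: Study Variables limits the 3-month PCL-5 and MFIS to those positive at baseline, so the plan must say which occasion that rule uses.
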